### Study settings and recruitments

2.4

This study will be carried out in Shaanxi Provincial Hospital of traditional Chinese medicine.CI subjects were mainly recruited from the wards and outpatient departments of Shaanxi Provincial Hospital of traditional Chinese medicine. At the same time, posters, leaflets, and routine free examinations will also help the recruitment of volunteers. In addition, the recruitment announcement on the official website of the hospital, official account of WeChat, micro-blog and other Internet media will help the volunteers to successfully recruit.

### Study group

2.5

Seventy-two CI subjects who met the inclusion criteria and signed the informed consent form were randomly divided into the experimental group and the control group according to the ratio of 1:1; 36 healthy people were recruited according to the inclusion criteria of the healthy control group.

### Study time

2.6

This clinical study will be conducted from August 1, 2020 to August 1, 2022.

### Interventions

2.7

The intervention measures designed in this study are based on TCM theory and professional practice knowledge. Relevant doctors have obtained the license issued by the national health and Family Planning Commission of China, and have received more than 3 years of clinical skills training in acupuncture and TMS. Patients in the experimental group and the control group were given basic treatment (sleep hygiene and cognitive therapy in CBT-I Technology); in addition, patients in the experimental group were given rMS treatment at HT7.

#### Experimental group

2.7.1

The rTMS therapeutic instrument (CCY-II, Wuhan yiruide medical products New Technology Co., Ltd., Wuhan) was used. According to the theory of traditional Chinese medicine, magnetic stimulation of left HT7 point was selected. After the preparation, the stimulation coil will be placed on the left HT7 acupoint (anteromedial wrist, radial to ulnar flexor tendon, on the metacarpal wrist fold) (Fig. 1). The setting parameters are: CTBS mode, total pulse number 1800,^[14]^ stimulation intensity 15%.^[15]^ Course of treatment: twice a day, with an interval of more than 4 hours, 5 days / wk, a total of 30 treatments.

**Figure 1 F1:**
[figure not shown]
Location of Shenmen (HT 7) Acupoint. Longxiang H. WHO standard acupuncture point locations in the Western Pacific region (Chinese-English bilingual edition) [M]. Beijing: People's Medical Publishing House, 2010.^[16]^

#### Control group

2.7.2

The control group was only given basic treatment.

#### Healthy control group

2.7.3

There was no intervention during the study period.

### Adverse events observation

2.8

Local skin numbness around HT7 point may be related to rMS of HT7 point. During the study, a patient treatment log will be established to monitor all adverse reactions during treatment and follow-up, and appropriate intervention will be carried out.

Patients with severe insomnia during the study were given dexzopiclone (3 mg QN). However, subjects who could not tolerate 80% of the rMS intensity and / or took more than twice a week of dexzopiclone were considered withdrawn.

In case of serious adverse reactions during the treatment, report to the principal investigator immediately, record the details in the patient treatment log and take corresponding treatment measures. If the subject or researcher thinks that the patient cannot tolerate these adverse reactions, the trial can be terminated and the subject will withdraw from the study.

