#### Withdrawal criteria

2.3.5

1.Violation of inclusion criteria and clinical trial protocol or exclusion criteria;2.Less than 30 sessions of RMS treatment were performed within 20 days;3.Serious adverse events occurred;4.Lost follow-up;5.Withdrawal of consent by subject or legal representative;6.Increase the treatment that may affect the study without the permission of the investigator.

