### Randomization

2.12

This study is a randomized controlled open trial. The method of randomization and allocation concealment is to generate 72 serial numbers according to the order of visit. The first group was randomly assigned to the first group, and the second group was randomly assigned to the last group. The randomized grouping scheme was kept in a sealed envelope, and the envelopes were opened in turn according to the order of admission, and the grouping of patients was determined according to the allocation scheme in the envelope.

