### Statistical analysis

2.13

According to the situation of data collection, data analysis will be based on the principle of intention to treat analysis and / or per protocol analysis. We will also evaluate the group effect by comparing the analysis results of the above 2 data sets to evaluate the accuracy of our analysis results.

All data will be analyzed by third-party statisticians using SPSS 23.0 (v23.0, SPSS Inc, Chicago, IL). *P* < .05 was significant. Descriptive statistics will be carried out by group and time for average, standard deviation, maximum value, minimum value, and so on.

The data in accordance with the protocol set were selected for analysis. If the data obey normal distribution, they can be described by means, and standard deviation. If the variance is uniform, the analysis of variance of complete random design can be used to compare the effect indexes. If the variance is not uniform, the rank sum test of multi group comparison of complete random design can be used. If the data does not obey normal distribution, it can be described by median and interquartile distance. The hypothesis test used the bilateral test uniformly, with *P* < .05 as the statistical significance.

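### Withdrawal rules that fall unequally on the arms, followed by selection of the protocol set, can leave the main comparison unprotected by randomisation

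*Protocol article*

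**What the plan says.** Section 2.12 states "This study is a randomized controlled open trial". Section 2.7.2 gives the comparator: "The control group was only given basic treatment". Controls therefore have neither stimulation nor a sham.

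Three events after randomisation lead to withdrawal:

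- Section 2.3.5 lists "Less than 30 sessions of RMS treatment were performed within 20 days".
- Section 2.8 adds two more in one sentence: "subjects who could not tolerate 80% of the rMS intensity and / or took more than twice a week of dexzopiclone were considered withdrawn".

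The course itself, in section 2.7.1, is "twice a day, with an interval of more than 4 hours, 5 days / wk, a total of 30 treatments".

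On the analysis set, section 2.13 first names "intention to treat analysis and / or per protocol analysis". It goes on: "We will also evaluate the group effect by comparing the analysis results of the above 2 data sets". Two paragraphs later it says "The data in accordance with the protocol set were selected for analysis".

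**The concern.** Randomisation makes the two arms comparable as allocated. Each of these rules removes patients because of something that happened afterwards, and that event is linked either to the stimulation or to sleep. Stimulation is what distinguishes the arms. Sleep is what the treatment may change, and it is also measured as a secondary outcome. Because allocation is known, the decision to ask for or give the rescue hypnotic may also differ by arm.

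If the arms lose different numbers or kinds of patient and the remaining patients supply the main result, a difference in the 1-back, complex figure or Hanoi tower scores can reflect who was left as well as what the treatment did. Section 2.10 has the causes of dropout recorded. That would reveal an imbalance but would not replace the missing cognitive scores.

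**Working it through.** **1. The plan's own figure.** Section 2.11 starts from 30 per arm with 20% loss: 30 × 1.20 = 36 per arm, 72 in total. This reproduces (dividing instead gives 30 / 0.80 = 37.5, so 38). The point does not rest on it. It supplies the arm size of 36 and the planned loss of 36 − 30 = 6 per arm.

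**2. Which arm each rule can reach.**

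| Rule | Section | Experimental | Control |
|---|---|---|---|
| Fewer than 30 sessions in 20 days | 2.3.5 | yes | not in practice (no stimulation) |
| Cannot tolerate 80% of intensity | 2.8 | yes | no (no stimulation) |
| Rescue more than twice a week | 2.8 | yes | yes, through sleep after randomisation |

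**3. Margin in the session rule.** Twenty days are two weeks and six days. At 5 treatment days a week that is at most 5 + 5 + 5 = 15 days, and 15 × 2 = 30 sessions. The rule requires 30, so the planned course has 30 − 30 = 0 spare.

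**4. What zero margin could mean.** Assume that no make-up sessions are allowed and that each session is missed independently with probability p. Neither the assumptions nor the values of p come from the article. The chance of falling below 30 is 1 − (1 − p)^30:

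- p = 0.5%: 0.140, or 5.0 of 36
- p = 1%: 0.260, or 9.4 of 36
- p = 2%: 0.455, or 16.4 of 36

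The range is 14% to 45% of the experimental arm. It is lower if misses cluster by day or by patient, or if they can be made up.

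**5. Effect on the contrast.** Let removed patients differ from those kept by d standard deviations, with the same d in both arms, and let m be the net difference in removals. The shift is about d × m / 36, with sign unknown. For d = 0.25 to 1 (assumed):

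- m = 1: 0.007 to 0.028 SD
- m = 6: 0.042 to 0.167 SD
- m = 16: 0.111 to 0.444 SD

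The standard error with 36 per arm is √(2/36) = 0.236 SD (√(2/30) = 0.258 with 30 per arm).

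**6. A second illustration.** Suppose there is no true effect, the worst sleepers are the ones removed, and the cognitive score correlates 0.3 to 0.5 with sleep severity. Removing 10% of one arm and 30% of the other shifts the difference by 0.09 to 0.15 SD. In 6,000 simulated trials per setting with 36 randomised per arm, a two-sided 5% t-test rejected in 6.6% and 8.9% of trials. With 20% removed from each arm at correlation 0.3 there was no bias, and it rejected in 4.9%. The favoured arm is the one that loses more poor sleepers.

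**The case against.** **Intention to treat is named and the two sets will be compared.** This is true, and a reader who inferred that the plan abandons intention to treat would go too far. But the and/or wording does not commit to it, and the later sentence selects the protocol set. What stands against the plan is that the as-randomised comparison is not made to lead. The article may leave day-20 testing of withdrawn patients to the full protocol, so its silence on that is not counted as a fault.

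**One missed session need not mean withdrawal.** A reader might infer that it must, or that a Monday-to-Friday clinic makes 30 sessions impossible except from a Monday start (28 fit from any other weekday). The documents do not support either as stated. They fix no weekdays and neither allow nor forbid make-up sessions, and 15 treatment days in 20 leave 5 other days. Both readings, and the 14% to 45% range, are conditional.

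**The intensity rule may remove few patients.** If the percentage refers to the 15% setting in section 2.7.1, the threshold is 0.80 × 15% = 12%. The article describes the stimulation as pain free and expects only local numbness. This stands, so the rule probably carries the least weight of the three.

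**The rescue limit has a reason.** The Introduction says oral hypnotics may worsen cognition, the limit applies to both arms, and the Discussion calls the study a pilot. That supports excluding heavy rescue users from a per-protocol set. It does not support removing them from the randomised comparison.

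**The illustrated bias is mostly below one standard error.** This also stands. Only the largest imbalance combined with a large d exceeds it. The common d is a simplification too, because patients who miss sessions and patients who need rescue are different kinds of patient.

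**Conclusion.** The point holds as a badly fixed rule. Two withdrawal rules act in practice on the experimental arm alone, the third depends on sleep after randomisation, and section 2.13 does not make the as-randomised comparison primary before it selects the protocol set. This follows from the text without any assumption.

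The direction and size of the bias do not follow from the text. A reader might infer that the rules favour the experimental arm. The article gives no rates of rescue use, intolerance or attendance, and the rules can pull in opposite directions: if stimulation helps sleep, the rescue rule removes more controls, while the other two remove only experimental patients. At a net imbalance of 6, equal to the planned loss in one arm, the illustrative shift of 0.04 to 0.17 SD is below the standard error of 0.24 SD. That is a moderate distortion of unknown sign. It justifies an amendment but is not evidence that the result will be wrong.

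**What to change.** - In section 2.13, name the comparison of all 72 randomised patients with insomnia, by allocated arm, as primary, and the per-protocol analysis as the sensitivity analysis.
- In sections 2.3.5 and 2.8, make the session, intensity and rescue rules reasons to leave the per-protocol set only, not the trial.
- Test every randomised patient who still consents at day 20, including those who meet one of the three rules.
- Report rescue use by arm.

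The cost is a short amendment to three sections and some additional day-20 tests at a visit already planned. The downside is that the primary estimate will then include any effect of the rescue hypnotic on cognition and of incomplete courses. The per-protocol analysis remains available for the narrower question.

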### Primary outcomes

2.9

The cognitive function of the patients was evaluated on the day of enrollment and the 20th day after treatment:

1.1-back working memory;2.Rey osterieth complex figure test;3.Hanoi tower test.

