**Methods/Design::**

This is a randomized controlled clinical trial. Seventy-two subjects aged 18 to 65 years old with primary insomnia and more than 3 months were randomly divided into 2 groups according to the ratio of 1:1, and 36 healthy controls were included. The control group was given sleep hygiene and cognitive therapy in behavioral cognitive therapy technology, while the experimental group was given the behavioral cognitive therapy technology intervention and magnetic stimulation of HT7 acupoint for 30 times (2 times / d, 5 times / wk for 20 days), while the healthy control group had no intervention measures. Before treatment and 20 days after treatment, we evaluated the working memory (1-back test), episodic memory (Complex Figure Test), and problem-solving ability (Hanoi tower test) processed by prefrontal lobe to explore the effect of magnetic stimulation on cognitive function of CI and its possible mechanism. At the same time, insomnia severity index was used to evaluate sleep state, Becker depression scale was used to evaluate depression, and Beck anxiety scale was used to evaluate anxiety. Chi-squared test or rank sum test was used to collect the data of patients. If *P* value is less than or equal to .05, the difference will be considered statistically significant.

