**Conclusion::**

This study explored the effect and mechanism of magnetic stimulation of Shenmen (HT7) on cognitive function of CI, and confirmed that magnetic stimulation of HT7 can be used as an alternative therapy to improve cognitive impairment of CI.

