### Estimation of sample size

2.11

The sample size was the minimum number of 30 cases in clinical trials. Considering the loss rate of 20%, 36 cases of N1 = N2 = 72 cases were selected in this study, and 36 cases of healthy controls were included.

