#### Primary outcomes

2.13.1

On the day of admission and the 20th day of treatment, the patients will be evaluated with

1-back working memory,

Rey osterieth complex figure test and

Hanoi tower test, and the obtained data will be used by rank sum test or Chi-squared test.

After statistical analysis between groups, the significant influence between groups will show that the 1-back working memory, Rey osterieth complex figure test, Hanoi Tower test there are differences.

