## Discussion

3

Sleep is an important part of human life activities. It can eliminate fatigue, enhance immune function, regulate emotion, and regulate cognitive function. Ci can not only lead to sub-health status, but also lead to damage in many cognitive fields, which brings serious harm to patients and society. No matter whether CI has cognitive impairment or not, cognitive function has been impaired to a certain extent.^[2]^

Neurocognitive deficits after CI are caused by neurobiological changes.^[17]^ Compared with healthy people, the regional homogeneity of the upper right medial prefrontal cortex was significantly different in CI patients; and the more serious the cognitive impairment, the greater the homogeneity difference of the dorsolateral cortex of the right prefrontal cortex.^[18]^ A voxel based fMRI morphometric study found that the volume of the left orbitofrontal Gray matter in insomnia patients decreased, and it was closely related to the subjective severity of insomnia.^[19]^ The microstructure of prefrontal cortex in insomnia patients is damaged, which affects the emission of brain nerve impulses and signal transmission, resulting in insufficient activation of cognitive processing and dysfunction of brain functional connectivity, which may be an important neurobiological process of Ci and its accompanying cognitive impairment.

RTMS and traditional Chinese medicine acupuncture and moxibustion are commonly used in CI treatment, and have significant curative effect. Compared with rTMS, RMS has fewer contraindications. Compared with acupuncture, RMS has the advantages of noninvasive and painless, which can reduce the pain of patients and increase the compliance of patients. In this study, rMS was combined with acupuncture and moxibustion of traditional Chinese medicine, and HT7 was used to intervene cognitive impairment of CI. The purpose of this study is to observe the clinical efficacy of magnetic stimulation of HT7 on cognitive impairment in patients with CI through the evaluation of cognitive function, sleep quality, and emotion of CI patients, and analyze the possible mechanism.

Our scheme is only a pilot study, so there may be problems in sample size and observation time. In the course of the experiment, we will try our best to reduce the deviation that affects the research results. Finally, we intend to confirm that magnetic stimulation of HT7 can be used as an alternative therapy to improve cognitive impairment of CI.

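### Three equal primary cognitive tests, each at two-sided P < .05, feed one claim of cognitive improvement with no stated success rule

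*Protocol article*

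**What the plan says.** Protocol article, section 2.9, lists the primary outcomes as "1.1-back working memory;2.Rey osterieth complex figure test;3.Hanoi tower test". They are measured at enrolment and on day 20. None is ranked above the others and no composite is formed.

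Section 2.13 sets the criterion for all testing: "The hypothesis test used the bilateral test uniformly, with *P* < .05 as the statistical significance". The Abstract puts it slightly differently, calling a difference significant if the P "value is less than or equal to .05, the difference will be considered statistically significant". The two wordings differ only at exactly .05, which does not affect this point.

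Section 2.13.1 applies a rank sum or chi-squared test to the primary outcomes and states the inference: "the significant influence between groups will show that the 1-back working memory, Rey osterieth complex figure test, Hanoi Tower test there are differences".

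The claim to be drawn is a single one. The Discussion says "we intend to confirm that magnetic stimulation of HT7 can be used as an alternative therapy to improve cognitive impairment of CI", and the Abstract's Conclusion says the study "confirmed that magnetic stimulation of HT7 can be used as an alternative therapy to improve cognitive impairment of CI". The same paragraph of the Discussion also says "Our scheme is only a pilot study, so there may be problems in sample size and observation time".

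**The concern.** Three chances at a 5% result serve one conclusion about cognition. The article fixes the threshold for each test but not how three results become one answer. One significant test and two null ones could be reported as success or as failure, and either would be consistent with the text.

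If the lenient reading is adopted once the results are known, the headline claim no longer carries the 5% error rate that section 2.13 suggests. This matters because the article says it intends to confirm efficacy.

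**Working it through.** **Inputs**
- Number of primary tests: 3 (section 2.9).
- Level per test: .05 two-sided (section 2.13), so .025 in the direction favouring HT7.
- Size of the randomized arms: 36 each, built up from 30 with a 20% loss rate (section 2.11).
- Correlation among the three test statistics: not given. It is assumed equal for all pairs and varied from 0 to 0.9.

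**The plan's own figure.** The article states no family-wise error rate. The only related figure that can be reproduced is the arm size: 30 × 1.20 = 36. Section 2.11 explains the 30 only by convention ("The sample size was the minimum number of 30 cases in clinical trials"), with no effect size, power or alpha behind it. The sample size therefore does not show which success rule was meant.

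**Step 1: independent tests, any one sufficient**
- Either direction: 1 − 0.95³ = 1 − 0.8574 = 0.1426, or 14.3%.
- Favouring HT7 only: 1 − 0.975³ = 1 − 0.9269 = 0.0731, or 7.3%, against 2.5% for a single test.

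**Step 2: correlated tests, any one sufficient.** Three equally correlated normal test statistics, no true effect on any test:

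| Assumed correlation | Any false difference | Any false result favouring HT7 |
|---|---|---|
| 0 | 14.3% | 7.3% |
| 0.3 | 13.6% | 6.8% |
| 0.5 | 12.5% | 6.3% |
| 0.7 | 10.9% | 5.5% |
| 0.9 | 8.4% | 4.2% |

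These come from numerical integration. A simulation of 2,000,000 draws agrees to within 0.1 percentage point (12.6% at 0.5).

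**Step 3: all three required.** With no true effect on any test, the chance that all three are significant is between 0.01% (correlation 0) and 2.3% (correlation 0.9). Under this rule there is no inflation.

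**Step 4: with adjustment.** With no true effect on any test, Holm makes at least one rejection exactly when the smallest p-value is at or below .05/3 = .0167. If independent, that chance is 1 − (1 − .0167)³ = 4.9%. At correlation 0.5 it is about 4.5%. Holm keeps the family-wise rate at or below 5% whatever the correlation.

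**Step 5: cost in power.** Difference detectable with 80% power, two-sided two-sample t-test, in SD units:

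| Per arm | At .05 | At .0167 |
|---|---|---|
| 36 | 0.67 | 0.78 |
| 30 | 0.74 | 0.86 |

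The t-test stands in for the planned rank sum test, so these are approximate.

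**The case against.** The strongest reply is that this is largely a matter of what is not said. The article is condensed, and a statistical analysis plan that is not shown could hold the success rule and the choice of score for each test. The choice of score can fairly be left there. The threshold is different. Section 2.13 does not defer it but sets P < .05 for every test, and 2.13.1 gives its own inference from significance. An adjustment made elsewhere would have to be reconciled with that text.

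A second reply is the pilot label, which does soften the point. But the same paragraph states an intention to confirm efficacy. If the trial is exploratory, the confirmatory wording should go. If it is confirmatory, the error rate needs control. The past tense of the Abstract's Conclusion adds little, because the article mixes tenses throughout.

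A third is that the Abstract ties each test to its own ability (working memory, episodic memory, problem solving), so separate claims are conceivable. The claim actually stated, however, concerns cognitive impairment as a whole.

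A reader might go further than the text allows in three ways:
- **That one significant test is the written rule.** It is not. Section 2.13.1 names the three tests together and fits an any-one or an all-three reading.
- **That a false finding of improvement has a 13–14% chance.** That range counts false differences in both directions and needs weak correlation.
- **That several scores per test raise the error further.** No section names the scores, so no figure for this can be supported.

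**Conclusion.** The point holds in limited form. Three equal primary tests at an unadjusted .05 support one global claim, and the article states no success rule.

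The size depends on two assumptions: that any one significant test would be taken as enough, and how strongly the tests are correlated. On the any-one reading, the chance of at least one false significant difference runs from 14.3% (independent) to 8.4% (correlation 0.9), above 5% over the whole range examined. In the direction favouring HT7 it runs from 7.3% to 4.2%, against 2.5%. The inflation is nearly threefold only if the correlation is weak. On an all-three reading there is none. The defect is that the text does not settle which reading applies. It should be corrected before the data are analysed.

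**What to change.** Replace the inference sentence in section 2.13.1 with wording such as:

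> One score per test is specified before the data are examined. The three p-values for experimental versus control are adjusted by Holm's procedure at a family-wise level of .05. A cognitive benefit is claimed only for tests that are significant after adjustment. All three differences are reported with 95% confidence intervals.

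The Discussion and the Abstract's Conclusion should then limit the claim to the tests that pass. Holm works on p-values, so the planned type of test need not change. Unadjusted 95% intervals may exclude zero for a test that fails after adjustment, and the report should say so where it happens.

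The change is to wording only, with no effect on patients, visits or procedures. The cost is power for each test: at the strictest Holm step the detectable difference rises from about 0.67 to 0.78 SD with 36 per arm, or from 0.74 to 0.86 SD with 30. Adjusting for baseline scores should not be counted as paying for this. It is not part of the wording above, and it would sharpen unadjusted testing equally. The planned tests of the secondary scales can stay as they are.
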